## Abstract

**Background:**

The increasing number of patients with chronic diseases represents a challenge for health care systems. The Chronic Care Model suggests a multi-component remodelling of chronic disease services to improve patient outcomes. To meet the complex and ongoing needs of patients, chronic disease prevention and management (CDPM) has been advocated as a key feature of primary care producing better outcomes, greater effectiveness and improved access to services compared to other sectors. The objective of this study is to evaluate the adaptation and implementation of an intervention involving the integration of chronic disease prevention and management (CDPM) services into primary health care.

**Methods/Design:**

The implementation of the intervention will be evaluated using descriptive qualitative methods to collect data from various stakeholders (decision-makers, primary care professionals, CDPM professionals and patients) before, during and after the implementation. The evaluation of the effects will be based on a combination of experimental designs: a randomized trial using a delayed intervention arm (n = 326), a before-and-after design with repeated measures (n = 163), and a quasi-experimental design using a comparative cohort (n = 326). This evaluation will utilize self-report questionnaires measuring self-efficacy, empowerment, comorbidity, health behaviour, functional health status, quality of life, psychological well-being, patient characteristics and co-interventions. The study will take place in eight primary care practices of the Saguenay region of Quebec (Canada). To be included, patients will have to be referred by their primary care provider and present at least one of the following conditions (or their risk factors): diabetes, cardiovascular diseases, chronic obstructive pulmonary disease, asthma. Patients presenting serious cognitive problems will be excluded.

**Discussion:**

In the short-term, improved patient self-efficacy and empowerment are expected. In the mid-term, we expect to observe an improvement in health behaviour, functional health status, quality of life and psychological well-being. At the organizational level, the project should lead to coordinated service delivery, improved patient follow-up mechanisms and enhanced interprofessional collaboration. Integration of CDPM services at the point of care in primary care practices is a promising innovation in care delivery that needs to be thoroughly evaluated.

**Trial registration:**

ClinicalTrials.gov Identifier: NCT01319656

## Background

The last decades have seen dramatic shifts in the pattern of diseases from infectious diseases to the current leading causes of mortality dominated by chronic diseases (CD) accounting for 59% of annual deaths and 46% of the global burden of disease [1]. Research suggests that complex chronic conditions such as diabetes, cardiovascular and respiratory diseases will impose an even larger burden in the future [1,2]. This represents a challenge for the health care system. While traditional health care funding and management are mainly designed to address acute health conditions, the bulk of health funds are allocated to patients with CD who are the heaviest users. In Canada, it is estimated that 42% of total direct medical care expenditures ($39 billion) are used each year to treat people with CD [3]. Due to lack of coordination of care and difficulties accessing services, patients with CD are disadvantaged in the current health care system and are, together with physicians, decision-makers and the general population, looking for fundamental changes. Several solutions have been proposed at the organizational and patient level.

From an organizational point of view, it has been demonstrated that a strong primary health care system is associated with better health indicators and more sustainable costs [4-9]. A recent report of the Canadian health care authorities has put forward the added-value of a strong primary health care system recognizing the role of primary care as a pivotal organization ensuring proper use of professional skills in the management of chronic diseases [10]. However, patients with CD represent a greater challenge to primary health care as they are associated with high health care costs and poor compliance to treatment and recommendations [11-13]. In the presence of CD, primary health care providers face difficulties in applying guidelines [14,15] and in maintaining care continuity [16]. To prevent potential health care system gaps in quality, efficiency, and effectiveness, the Chronic Care Model (CCM) has been suggested as a promising solution. Hence, the integration and application of the CCM into primary care organizations should be supported [17,18]. Although various stakeholders do agree on the relevance of the CCM approach, translating its conceptual clusters into operational strategies is a complex undertaking. Consequently, decision-makers and physicians have to consider reliable evidence-based evaluations to improve quality of care and to manage allocation of resources as efficiently as possible [19].

Lifestyle-related risk factors of CD, such as obesity, physical inactivity and diet-related behaviours, have been linked to increased risks of morbidity and mortality [20]. This reflects the 40% of CD that can be prevented [21]. To meet the complex needs of patients with chronic conditions seen in primary care, these settings may benefit from being able to offer a range of chronic disease prevention and management (CDPM) services under one roof. Such integrated services have been identified as a potential key to fulfilling standards of care for patients with CD. To prevent primary health care clinics from operating in isolation, CDPM services have to be provided by an interdisciplinary team in coordination with primary care. Interdisciplinary teamwork has been associated with a higher use of preventive strategies and a lower burden for caregivers [22]. Primary care physicians are in the best position to coordinate these strategies as they see patients more frequently and at earlier stages of the disease than specialists. In the search for strategies that might help reduce the burden of CD and related high risk lifestyles, resource utilization and management schemes deserve to be evaluated. This makes evaluation an integral part of the implementation process.

In the Saguenay-Lac-Saint-Jean region of Québec (Canada), health care professionals have been mobilized to deal with the challenges of CD management through the introduction of integrated CDPM services. Since 2001, a strong network of CDPM services has been deployed in the six health care centers across the region. The approach groups together various CD based on common CDPM services, with a range of standardized services rooted in evidence-based medicine and integrated at the local level into each of the six regional territories [23,24]. The program addresses a number of CD, including cardiovascular disease (CVD), heart failure, chronic obstructive pulmonary disease (COPD), asthma and diabetes, and aims to: (1) reduce and correct modifiable risk factors; (2) strengthen individual self-efficacy; (3) optimize functional autonomy, biopsychosocial balance and health; and (4) support self-management [23]. The program offers a range of activities (educational, counselling, follow-up) delivered by various professionals on aspects such as compliance with medication/vaccination, nutrition, physical activity, smoking cessation, stress management and psychosocial support [23]. The variety of services for a given patient are scheduled over a six-month period and may include individual or group meetings [25]. The program intervention principles are based on complementary theoretical models: McGill’s nursing conceptual model [26,27], the PRECEDE model [28,29], and the Prochaska & DiClemente stages of change model [30,31]. However, collaboration between this network and the primary care providers has so far not been optimal for several reasons and consequently the services have not reached a large part of the population with CD. Services were offered to people mainly after an acute episode of care or hospitalization.

The Cochrane Collaboration published a review of the effectiveness of care and services shared between primary care services and specialized care for CD management; however it was not possible to draw conclusions regarding the effectiveness of integration interventions in this field at the time [32]. Theoretically, this kind of shared care model presents an opportunity to provide patients with the benefits of specialist intervention combined with continuity of care and management of comorbidity more easily offered through primary care whose providers maintain responsibility for all aspects of patient health care beyond a single specific CD. In this regard, a recent Canadian experience with interventions involving close collaboration between primary care settings and CD management services stressed the desirability of this integration [33,34]. The implementation in Alberta of an integrated services network within primary care settings, based on close collaboration with specialized services, demonstrated a positive impact on patients, professionals and the organization of services. However, the total effects of this intervention are still being investigated.

CDPM has been shown to be effective in the context of CVD [35], COPD [36], asthma [37] and diabetes [38]. Usually offered in specialized settings, such interventions have had different outcomes such as a decrease in the use of health services, and improved functional status and quality of life, most often in the short term. Overall, these studies were conducted outside primary care practices and were limited in time. Intervention models and theoretical foundations underlying these programs are varied, but most often were founded on a patient education intervention conducted by different health professionals specialized in CD and focused on supporting the modification of risk factors and self-management.

To date, the appropriateness of using multidisciplinary specialized professionals in the context of primary care practices has been little studied. The few studies found were conducted along the same lines as that of specialized CD interventions, that is, in the context of a single disease, such as COPD and asthma [39], metabolic syndrome [40], kidney failure [41], diabetes [42], or among people with risk factors [43]. Again, interventions were based on different approaches, mainly on self-management support and patient education. The outcomes used vary greatly from one study to another and include the use of services, quality of life, various physiological indicators and risk factor modification.

Among ongoing studies, Perula et al. published a study protocol of an open, two-arm parallel, non-pharmacological approach based on the promotion of a healthy diet and physical activity to control cholesterol levels among patients with hyperlipidemia in the context of primary care [44]. The intervention is based either on motivational interviewing or on the usual brief advice. The study will assess the degree of dietary and physical activity improvement, weight loss in overweight patients, adherence to treatment guidelines as well as lipid levels and cardiovascular risk.

This study aims to introduce a pragmatic innovation by adapting and integrating CDPM services into primary care settings and to propose an innovative combination of strategies to evaluate the effects and implementation of this intervention in eight primary care practices in the Saguenay region. The main components of this intervention are illustrated in the intervention logic model presented in Figure 1. The evaluation-specific objectives are to: (1) assess the implementation of a clinical intervention of CDPM services integrated into the existing structure of the primary care network in order to describe the implementation context, the implementation process and the satisfaction of those involved, including the perspective of patients; (2) measure the effect and the effectiveness of interventions among primary care patients. We hypothesize that patients receiving the intervention will report better empowerment and self-efficacy and will demonstrate reduced health risk behaviours.

**Figure 1 F1:**
[figure not shown]
Intervention logic model.

## Methods/Design

### Settings

The intervention will be implemented in the Saguenay region of Quebec (Canada) where primary care physicians work in two types of organizations principally: Group practices, involving a group of primary care physicians working in a team with no access to professionals from other disciplines; Family Medicine Groups, new organizations in which primary care physicians work with nurses at various degrees of collaboration and share the same patients and medical files. No other disciplines are involved in the practice. Both organizations provide care for a population including a majority of patients with chronic diseases and risk factors.

### Intervention

The clinical components of the intervention consist of many steps described in the logic model developed for this project (Figure 1). According to the needs expressed by primary care professionals, a number of patient-centered activities were developed. CDPM services were adapted to services and resources already in place with a focus on self-management support, patient-centered care, motivational interviewing, interprofessional collaboration and integration of services. Such a multi-dimensional learning package is designed to improve both process and outcome measures and increase intervention impact. This model has proven to be effective in the development of behavioural interventions in patients with CD [45]. Further detail on the intervention is provided in Table 1.

**Table 1 T1:** Characteristics of the interventions

**CDPM practitioner training**	Theoretical training on:
	− Motivational interviewing
	− Function of the respiratory system
	− Function of the cardiovascular system
	− Diabetes
	− Risk factors
	− Existing CDPM services
	Practical training:
	− Three-week mentoring in specialized CDPM services facilities.
**Preliminary clinical evaluation**	The clinical evaluation of participants includes:
	− Anthropometric characteristics
	− Medical history
	− Medication
	− Functions (respiratory, cardiovascular, endocrine, gastro-intestinal)
	− Lifestyle habits and risk factors
	− Patient preoccupations and objectives
	− Previous interventions (nutrition, physical activity, respiratory, smoking cessation)
	− Recent changes (weight, alcohol consumption)
**Disciplines involved in the intervention**	The interventions, based on a referral from a family physician or nurse, are provided by professionals in the following disciplines:
	− Clinical coordination
	− Nursing
	− Physical activity therapy
	− Nutrition
	− Respiratory therapy
	− Smoking cessation therapy
**Implemented interventions**	The interventions implemented are:
	− Self-management support
	− Education on diseases (diabetes, COPD, asthma, cardiovascular)
	− Education on risk factors (pre-diabetes, high blood pressure, dyslipidemias, obesity, physical inactivity, smoking)
	− Counseling on medication
	− Motivational interviewing
	− Education about nutrition
	− Education about physical activity
	− Counseling on smoking cessation
**Tools and support material**	Each intervention is supported by print and other material to ensure that patient engagement is maintained even between the interventions. These include documents on:
	− Chronic disease management
	− Asthma, COPD
	− Diabetes
	− Cardiovascular
	− Metabolic syndrome
	− Hypo/hypertension
	− Tools for smoking cessation
	− Stress management
	− Blood pressure monitoring journal
	− Personal objectives journal
	− Physical activity journal
**Communication & coordination**	The CDPM practitioners in our study work within primary care settings which enhances communication with primary care physicians, nurses and staff. The clinical coordinator ensures optimal communication and transition of care between the project team, the primary care professionals and specialized services. Special attention is given to the distinction of tasks fulfilled by project CDPM practitioners and tasks fulfilled by primary care nurses.
**Integration**	Prior to the implementation of interventions, a pre-implementation evaluation is conducted to identify the needs for CDPM services and the contextual factors of the participating PC clinics in the follow-up of CD patients. The pre-implementation evaluation of the project promotes the sharing of a common positive vision of an intervention that focuses on prevention, earlier support for patients in the course of their disease, interprofessional collaboration, services integration, motivational interviewing and self-management support.
**Participating primary care professionals**	Participating primary care professional include:
	− Family physicians (63)
	− Nurses (5)
	Participating primary care settings:
	− Four (4) clinics
	− Four (4) family medicine groups
**Participating specialists**	Participating specialists include:
	− Cardiologists
	− Internal medicine specialists
	− Endocrinologists
	− Pneumologists

The intervention will be implemented using support mechanisms and ongoing evaluation within the participating clinics to ensure a harmonious integration. Interventions at the patient level will: (a) be patient-centered and educational in nature; (b) last less than three months and involve at least three encounters with CDPM practitioners; (c) include individual interviews or patient focus groups involving close relatives. The intervention will consolidate the central role of primary health care professionals and their organizations, while maintaining the natural proximity between the patient and his or her family physician. In this regard, interventions will: (a) be carried out upon referral from the primary care team; (b) allow an exchange with the primary care team and will be recorded in primary care medical records; (c) return the responsibility of long-term follow-up to the primary care team.

### Evaluation

Consistent with the logic model (Figure 1), the evaluative approach will focus both on the implementation of the intervention and the measurement of its effects by using a mixed methods design [46] to evaluate health interventions [47]. The implementation evaluation will involve descriptive qualitative methods, while the evaluation of the effects will be based on quantitative methodology. This combination of approaches used concomitantly aims to deepen our understanding and to corroborate the evaluation results.

#### Implementation evaluation (objective 1)

Implementation evaluation consists in investigating the relationship between an intervention and its context during implementation [48]. It will be based on two approaches: a realistic evaluation, aiming to explain how various contexts influence observed effects [49], and a participatory evaluation aiming to determine the elements that could potentially inform and help improve future interventions and decision-making [50]. A realistic evaluation recognizes that any effect (E) of an intervention arises from the interaction between the intervention (I) and the context of its deployment (C). It aims to highlight the underlying mechanisms as well as the way they operate under certain conditions. Information about these three elements (E, I and C) will be collected during all three stages of the implementation. Moreover, realistic evaluation recognizes that results can be apparent not only at patient-level but also at the level of the professionals and organizations involved [51].

The participatory evaluation approach will help to adapt both the data collection tools and the data analysis strategy in order to bring to light elements that can guide future intervention implementations.

Table 2 describes the implementation evaluation focus (context, intervention or effects) that consists of three phases (pre-, per- and post-intervention) and will be conducted among the five categories of partners involved in the project (decision-makers, n = 15; primary care physicians, n = 63; clinics, n = 8; specialists, n = 12; CDPM professionals, n = 20; patients and their families, n = 326). Patients (5 per clinic, total = 40) and their families (spouse or main family caregiver) will be invited to take part in focus groups.

**Table 2 T2:** Implementation evaluation

**Evaluated dimensions**	**Decision-makers**	**Primary care prof.**	**Specia-lists**	**CDPM prof.**	**Patients/family**	**Patient records**	**Project documentation**
**Pre-intervention stage**							
Description of settings (contextual factors) (C)	FG	FG	II	FG			
Needs analysis (C)	FG	FG	II	FG			
**Intervention stage**							
Identification of problems and difficulties (C)							Document analysis
Care and services for patients (I) (Intervention fidelity)						Checklist entry	
**Post-intervention stage**							
Extent of implementation/Services offered (I)				II		Data entry	
Opinion on the implementation process (C)	FG	FG		FG			
Description of effects on professionals/organizations (E)	FG	FG		FG			
Care and services for patients (I)				FG	FG		
Identification of barriers and facilitating factors (C)	FG	FG		II			
Satisfaction with intervention (E)	FG	FG		II	FG		

FG: Focus group; II: Individual interview; C: Context; I: Intervention and action mechanisms; E: Effects of the intervention at the patient, practitioner and organizational levels.

To ensure fidelity of the intervention and to prevent clustering, the intervention was designed by the research team. Nevertheless, in this regard the research team consulted with primary health care providers in each practice, specialists, and decision-makers to ensure that the intervention is adapted to the needs expressed. Moreover, interventions will be done by CDPM professionals, recruited and trained by the research team about the general principles of self-management support, patient-centered care, motivational interviewing, interprofessional collaboration and integration of services. The rationale of such a process is to ensure standardization of practices within and across the eight clinics in order to prevent study interventions from evolving differently, as results will be unusable if participants experience different interventions. However, despite the use of such patterns, heterogeneity that may be observed and documented between clinics in terms of outcomes produced, termed “center effects” is part of the pragmatic design and will reflect the clinical reality of primary health care. It has been suggested that interventions may be affected by center-specific issues and characteristics such as degree of sub-specialization within practices and provider background and experience, [52] however, we believe that delivering interventions by practitioners who evolve through the same training process will reduce clustering effects so that the experiment can be replicated across centers and over time [53]. This desired objectivity is based on the involvement of systematic recourse to the collective production of evidence and requires standardization of practices within settings in order to produce replicable findings which can then be used to standardize practice within, and across, clinical care settings [54]. Moreover, efforts will be made to increase the number of participants in each setting in order to reach a certain degree of comparable statistical weight for every practice. Throughout the implementation phase, information about interventions offered to each patient will be collected with a standardized checklist filled out by the CDPM professionals after each appointment to ensure the fidelity of the intervention [55].

This study includes an evaluation process that measures the integrity and feasibility of the implementation interventions and clinical interventions that will be used. Furthermore, the study will assess how the interventions are executed, will distinguish between components of the interventions, and will identify contextual factors that may influence the content and effectiveness of the implementation intervention. The process evaluation will also examine how well the interventions were adapted to local barriers and facilitators.

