#### Evaluation of effects (objective 2)

Effects will be assessed using three different strategies. To measure short-term effects, a pragmatic randomized experimental design with delayed intervention in the control group will be used [59]. The first step of randomization is the sequence generation using a simple random allocation sequence. The second step is allocation concealment by development and allocating concealment mechanism (sequentially numbered, sealed, opaque envelopes) followed by preparation of the allocation concealment mechanism using the sequence from step one. Research team members involved in generation and allocation concealment will be different from the team members involved in the implementation of assignments. Thus, the intervention group allocation system is set up so that the team member enrolling participants does not know in advance in which group the next person will be allocated.

Patients will be referred by primary care providers (family physician or nurse) to the research team who will be responsible for assessing eligibility and obtaining informed consent, as well as baseline measures (T1). For each study participant, a research assistant at the central office will open a numbered and sealed envelope. The card inside will tell if the patient will be in group A or in group B. This information will immediately be provided to the patient and subsequently to the clinical team in order to schedule the clinical interventions.

Because participants will be invited to receive the interventions in their usual clinics, blind randomization is not possible. Both patients and health care providers will know who is involved in each group, therefore we used independent (unmatched) random samples of patients to receive the intervention immediately after baseline assessments (Group A: immediate intervention group) or at the end of a three-month waiting period (Group B: delayed intervention group). We chose this randomization process because of the potential proximity of patients in and between clinics. In practice, however, we think that communication between patients of the same clinic or between clinics is scarce and will not pose a substantial threat for contamination.

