##### Data analysis

We will first describe participants’ characteristics in each group, using means and standard deviations for continuous variables, and percentages for categorical variables. The *t*-test (for continuous variables) and the chi-square test (for categorical variables) will be used to compare baseline characteristics across study groups.

To evaluate short-term effects, Groups A and B will be compared on T2 scores (continuous variables such as self-efficacy, health education impact) with an analysis of covariance (ANCOVA) adjusted for T1 scores [72]. If the groups differ at baseline despite randomization, the ANCOVA will also be adjusted for the relevant variables [73]. The independent variable “Group” will be tested for significance at the 5% level.

To document effects over a year, a repeated measures analysis of variance will be used to study the evolution of continuous variables collected three times in Group A [74]. Mid-term effects will be evaluated by comparing T3 measurements in Group A (modifiable risk factors, functional health status and psychological well-being) with the same variables measured in Group C (from the PRECISE cohort) using an ANCOVA adjusted for T1 scores and non-equivalent baseline characteristics (variables not used for matching) [73]. Since groups A and C will be matched on four variables only, they will be considered independently in the analysis. Again, the variable “Group” will be tested for significance at the 5% level.

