##### Sample size and statistical power

The required sample size for the randomized clinical trial was calculated for the two main variables (measured with the SEM-CD and the heiQ) with a two-sided α = 0.05 and 80% power. First, for continuous scores, 64 participants in each group will allow to detect a medium effect size (ES=0.5) [75]. In addition, for the heiQ, results are also expressed as the percentage of patients improving at least half a standard deviation. In a before–after study, 35% of patients receiving the intervention presented an improvement of this magnitude [69]. Using these data in a conservative scenario providing for improvement in 20% of control participants, 138 patients are required in each group to detect a 15% difference. Accounting for an anticipated drop-out rate of 15%, 326 patients will be randomized, 163 in each group. A smaller ES of 0.34 will thus be detectable for continuous scores.

Comparison of the 138 subjects in Group A, re-measured at T3 to the same number of subjects selected in the PRECISE cohort, will also allow detection of an ES of 0.34 when measuring mid-term effects (α = 0.05, power = 80%). An additional 15% will also be enrolled in anticipation of withdrawals.

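### The A-B analysis and power statement treat patients as independent, although at T2 delivery-related clustering can exist in Group A alone

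*Protocol article*

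**What the plan says.** - **Clustering is acknowledged.** Under Implementation evaluation (objective 1), in the text after Table 2, the article allows that outcomes may differ between clinics and accepts such centre effects as part of a pragmatic design. Its remedy is common recruitment and training: "we believe that delivering interventions by practitioners who evolve through the same training process will reduce clustering effects". It claims a reduction, not absence, and gives no ICC.
- **Delivery.** CDPM practitioners see each patient at least three times. Under Intervention, the contacts "include individual interviews or patient focus groups involving close relatives".
- **Timing.** Under Evaluation of effects (objective 2), Group B completes T2 just before its own intervention starts, so only Group A has been treated when the arms are compared.
- **Allocation.** Individual patients are allocated "using a simple random allocation sequence". No stratification by clinic is stated.
- **Analysis.** Under Data analysis, the arms are compared on T2 scores "with an analysis of covariance (ANCOVA) adjusted for T1 scores". Further covariates enter only if the groups differ at baseline. No clinic or practitioner term is named.
- **Power.** Under Sample size and statistical power, the calculation is made "with a two-sided α = 0.05 and 80% power". It concludes: "A smaller ES of 0.34 will thus be detectable for continuous scores".

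**The concern.** By T2, Group A patients share practitioners, clinics and possibly group sessions, whereas Group B patients have had none of this. Outcomes in A can therefore be correlated within a delivery unit while those in B are not, which is a partially nested design. An ANCOVA that treats all patients as independent understates the variance of the Group A mean. Intervals come out too narrow, and a test declared at 5% rejects a true null hypothesis more often than that.

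The A-B contrast is the only randomised evidence on effect in this study, so its significance level matters. The detectable effect size also rests on independence, an assumption that the article's own remarks on centre effects do not support.

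**Working it through.** **1. Reproduce the plan's figures under independence.** Inputs from Sample size and statistical power: two-sided α 0.05, power 80%, ES 0.5, 35% versus 20%, drop-out 15%.

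- ES 0.5: 64 per arm (t-based 63.8, rounded up). Agrees.
- 35% versus 20%: 138 per arm without continuity correction. Agrees.
- Drop-out: 138 / (1 − 0.15) = 162.4, so 163 per arm and 326 in total. Agrees.
- Detectable ES with 138 per arm: (1.960 + 0.842) × √(2/138) = 0.337, given as 0.34. Agrees.

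All four reproduce with no design effect, so none was used.

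**2. Clinic effect shared by both arms.** With individual allocation across eight clinics, the unclustered test was simulated (10,000 runs per setting). Type I error was 5.2%, 4.8% and 4.8% at ICC 0.02, 0.05 and 0.10. This form of clustering does no harm here.

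**3. Clustering in Group A only.** Two inputs are assumed. The ICC is taken as 0.02 to 0.05. The cluster is taken either as each of the 20 CDPM professionals counted for the implementation evaluation (m = 138/20 = 6.9) or as one team per clinic (m = 138/8 = 17.25). The article fixes neither.

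- Design effect in A: DE = 1 + (m − 1) × ICC
- Inflation of the variance of A − B: V = (DE + 1)/2
- Type I error: 2 × [1 − Φ(1.96/√V)]
- Detectable ES: 0.337 × √V
- Power at 0.34: Φ(0.34/√(2V/138) − 1.96)

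| Clusters | ICC | DE | V | Type I, formula | Type I, simulated | Detectable ES | Power at 0.34 |
|---|---|---|---|---|---|---|---|
| 20 | 0.02 | 1.118 | 1.059 | 5.7% | 6.1% | 0.347 | 78% |
| 20 | 0.05 | 1.295 | 1.148 | 6.7% | 7.0% | 0.361 | 75% |
| 8 | 0.02 | 1.325 | 1.163 | 6.9% | 7.2% | 0.364 | 75% |
| 8 | 0.05 | 1.813 | 1.406 | 9.8% | 10.0% | 0.400 | 66% |

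Under independence, power at 0.34 is 81%. The detectable sizes use normal quantiles; small-sample degrees of freedom would raise them slightly.

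**4. Does T1 adjustment repair the test?** No. Delivery effects arise after T1, so the covariate removes patient-level variance and leaves the cluster variance in place. Simulating the stated ANCOVA with an assumed T1-T2 correlation r = 0.5 gave type I error of 6.1% to 7.5% (20 clusters) and 7.6% to 10.9% (8 clusters) for ICC 0.02 to 0.05.

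**5. Can T1 adjustment restore the 0.34?** Possibly, because 0.34 takes no credit for it. If the ICC refers to the variance left after adjustment, break-even needs 1 − r² = 1/V, so r = √(1 − 1/V): 0.24 and 0.36 for 20 clusters, 0.37 and 0.54 for 8. If the ICC refers to total variance and T1 explains none of the cluster part, break-even is r = √(V − 1): 0.24 and 0.38, then 0.40 and 0.64. The article gives no T1-T2 correlation.

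**The case against.** **Individual randomisation removes clinic effects.** This stands for effects shared by both arms, as step 2 shows. A reader might infer that any clinic clustering makes the standard errors too small; the design does not support that. The problem is limited to correlation arising from delivery in Group A, including an intervention effect that varies by clinic.

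**The 0.34 is not shown to be optimistic.** This also stands. It is an unadjusted two-sample figure, the analysis adjusts for T1, and a moderate T1-T2 correlation could cover the loss. Nor did 0.34 set the sample size: 138 per arm came from 35% versus 20%, and the continuous target was ES 0.5. At ES 0.5, power is still about 94% in the worst row: Φ(0.5/√(2 × 1.406/138) − 1.96) = Φ(1.54). The net direction is unknown, so the 0.34 can be called incomplete but not wrong.

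**The cluster size is not known.** Correct. One team per clinic is an assumption, and the only head count in the article is 20 professionals. Patients meet several disciplines over at least three contacts, so membership may be multiple. For this reason both scenarios are shown.

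**Training mitigates clustering, and the random-effects form belongs in an analysis plan.** In part. Training may lower the ICC, but the article itself claims only a reduction. The exact covariance structure can be left to an analysis plan. The article, however, states the model and the detectable effect size, and both assume an independence that its own text puts in doubt.

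**Simple allocation.** A reader might count the lack of stratification by clinic as a flaw. It is not one: simple randomisation is valid, and even a 145:181 split (the ends of the 95% range for 326 patients) costs little efficiency, since 4 × 145 × 181/326² = 0.988.

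**Conclusion.** The point holds for clustering in Group A only. The stated ANCOVA would not keep its 5% level if outcomes correlate within practitioner or delivery team, or if the intervention effect differs by clinic. For an assumed ICC of 0.02 to 0.05, the actual level is about 6% to 7% with 20 clusters and about 7% to 10% with 8. These figures depend on the assumed ICC and cluster structure, neither of which the article gives. An ICC near zero would make the problem negligible, and fewer or larger clusters would worsen it. Adjustment for T1 may recover power but not the type I error. The change should be made: the randomised comparison depends on this test and the correction needs no extra patients.

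**What to change.** 1. **Analysis.** Compare A and B on T2 with T1 score and clinic as fixed effects, plus a random delivery-cluster effect in Group A only, using small-sample degrees of freedom. Define the cluster (practitioner or clinic team) before the data are examined, with a rule for patients seen by several professionals. The checklist completed after each appointment is the natural source; confirm that it records who delivered each contact.
2. **Power statement.** Say that 0.34 assumes independence. Beside it, give the assumed ICC range and the detectable effect size before T1 adjustment: about 0.35 to 0.36 for 20 clusters and 0.36 to 0.40 for 8, slightly larger with small-sample degrees of freedom. Add that T1 adjustment may offset this, depending on the T1-T2 correlation.
3. **Optional.** Prepare a separate blocked envelope series for each clinic. This is a cheap refinement and does not correct an error.

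The cost is analysis work, slightly wider intervals and a less favourable stated detectable effect size.
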